#### Outcomes

The primary outcome is the clinical success rate at one month after drainage. Clinical success is defined as reduction in the size of WON to < 2 cm. Within one month of the drainage, if the patient needs to change the treatment method (such as the additional placement of nasal cyst drainage tube; or the DPPS removed and replaced with a LAMS), it will be recorded as drainage failure. The secondary outcome is technical success, operation time, recurrence, AEs, and secondary interventions. The definitions of the primary and secondary outcomes are presented in Table 2.

**Table 2 Tab2:** Definitions of the primary and secondary outcomes

Outcomes	Description
Clinical success	The diameter of the WON ≤ 2 cm
Technical success	LAMS or DPPS deployed successfully
Operation time	Time duration from the beginning to the end of the EUS-guided stent implantation procedure
Recurrence	After successful drainage, cyst reappears on imaging examinations with symptoms requiring intervention
Adverse event	
Perforation	Imaging manifests as pneumoperitoneum with peritoneal irritation syndrome
Bleeding	Any bleeding that requires intervention, blood transfusion, and hospital observation
Suprainfection	Postoperative fever, increased inflammatory index (CRP, PCT), or positive blood culture
Occlusion	The stent is filled with tissue or debris
Migration	The stent is completely or partially displaced into the WON or stomach
Others	Adverse events that occurred in the trial but not described above
Secondary intervention	Any endoscopic operation after stent is placed

*CRP* C-reactive protein, *PCT* procalcitonin

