**Fig. 3 Fig3:**
[figure not shown]
Schedule of enrollment, follow-up, and assessments. Basline^0^: screening of laboratory tests can be accepted the previous week in our hospital inspection report. Stent removal^1^: time from stenting to postoperative withdrawal (33 ± 3 days). Blood routine^2^: hemoglobin (HGB), erythrocyte count (RBC), platelet count (PLT), leukocyte count (WBC), neutrophil percentage (%), lymphocyte percentage (%). Liver and kidney function^3^: alanine aminotransferase (ALT), aspartate aminotransferase (AST), total bilirubin, direct bilirubin (DBIL), indirect bilirubin (IBIL), alkaline phosphatase (ALP), glutamyl transferase (GGT), blood urea nitrogen (BUN), creatinine (Cr). Coagulation function^4^: prothrombin time (PT), fibrinogen (FIB), activated partial thromboplastin time (APTT), thrombin time (TT). Serum amylase^5^: assessed 3 h and 24 h after the operation. CT^6^: preoperative and postoperative enhanced CT examination, 3 months and 6 months postoperative CT examination. The primary endpoint^7^: immediate success rate of surgery, drainage success rate 1 month after surgery. Secondary endpoints^8^: the incidence of clinical complications, operation time, the recurrence rate of pancreatic pseudocyst within 1 month and 1 month after the operation, and secondary interventions

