#### Statistical considerations

##### Sample size

The sample size calculation is based on a literature review and conference discussion regarding the clinical success rate of LAMS or DPPS drainage for WON. The LVPWON trial is a superiority trial in which the sample size calculation was based on the assumption that the incidence of the primary endpoint with LAMS and DPPS is 90% and 75%, respectively. Assuming a one-side alpha (type I error) of 0.025 and a power of 85% (beta, a type II error, was taken as 0.15), we used the following formula to calculate sample size and found that 256 patients (128 per condition) would be necessary, including a possible dropout rate of 10%.

$$ n={\frac{\mu_{1-\alpha}\sqrt{2\overline{p}\left(1-\overline{p}\right)}+{\mu}_{1-\beta}\sqrt{p_T\left(1-{p}_T\right)+{p}_C\left(1-{p}_C\right)}}{{\left({p}_T-{p}_C\right)}^2}}^2 $$

In this formula, *p*_*T*_ represents expected success rate of the LAMS group, *p*_*C*_ indicates expected success rate of the DPPS group, $$ \overline{p} $$ is average success rate of the two groups, and *μ* represents the quantile of standard normal distribution.

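### Recurrence can occur only after successful drainage, which the stent itself influences, so comparing it between arms is not a randomised comparison; the Fig. 3 caption also gives it a lesion and window that do not fit the trial.

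*Protocol article*

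**What the plan says.** The Outcomes section of the protocol article lists recurrence among the secondary outcomes, and Table 2 defines it: "After successful drainage, cyst reappears on imaging examinations with symptoms requiring intervention". The row gives no time window and no denominator.

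The same section fixes when success is judged: "The primary outcome is the clinical success rate at one month after drainage". It adds a failure rule that begins "Within one month of the drainage, if the patient needs to change the treatment method"; such a patient is recorded as a drainage failure. The Sample size section assumes that the "incidence of the primary endpoint with LAMS and DPPS is 90% and 75%, respectively".

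The Fig. 3 caption describes the endpoint differently: "the recurrence rate of pancreatic pseudocyst within 1 month and 1 month after the operation". Table 1 admits patients with WON, and the Background treats pseudocyst drainage and WON drainage as separate topics. Data collection and follow-up schedules visits at one, three and six months, with a final CT later. The Fig. 3 caption lists CT at three and six months.

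**The concern.** A patient can recur only after first succeeding. Success comes after randomisation, and the trial is designed on the expectation that the stent changes it by 15 percentage points. The patients who can recur are therefore not two comparable random samples. If LAMS clears some collections that DPPS would not, those patients are at risk of recurrence in the LAMS arm only. The Discussion makes this plausible, because it argues that the larger diameter makes debridement possible.

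At stake is what the trial can say about durability. Recurrence is the only listed outcome that directly measures whether drainage lasts. A difference in it could reflect who succeeded rather than what the stent did afterwards.

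The caption adds a second problem. A reader cannot tell from it which lesion is counted, or over what period.

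**Working it through.** **Inputs from the document.** Success 90% (LAMS) and 75% (DPPS); one-sided alpha 0.025; power 85%; dropout 10%; 128 per arm; 1:1 allocation (Sample size, Study population). No recurrence rate is given, so every recurrence rate below is an assumption.

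**Reproducing the plan's figure.** With mean success 0.825:

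n = [1.960 × √(2 × 0.825 × 0.175) + 1.036 × √(0.90 × 0.10 + 0.75 × 0.25)]² / 0.15² ≈ 113.7, so 114 per arm.

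114 / 0.90 = 126.7, so 127 per arm and 254 in total. The plan says "256 patients (128 per condition) would be necessary", which agrees to within two patients. The planning rates can be taken at face value.

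**Patients who can recur.** 128 × 0.90 = 115.2 with LAMS; 128 × 0.75 = 96 with DPPS.

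**Denominator 1: successes only.** Assume three patient types: 75% succeed with either stent, 15% succeed with LAMS only, 10% with neither. Assume also that the stent has no effect on recurrence. Let a be the recurrence rate in the first type and b in the second. Then

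LAMS rate = (0.75a + 0.15b) / 0.90; DPPS rate = a.

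| a | b | LAMS | DPPS | Spurious excess (points) |
|---|---|---|---|---|
| 5% | 5% | 5.0% | 5.0% | 0 |
| 5% | 10% | 5.8% | 5.0% | 0.8 |
| 5% | 20% | 7.5% | 5.0% | 2.5 |
| 5% | 30% | 9.2% | 5.0% | 4.2 |
| 10% | 10% | 10.0% | 10.0% | 0 |
| 10% | 20% | 11.7% | 10.0% | 1.7 |
| 10% | 30% | 13.3% | 10.0% | 3.3 |
| 10% | 40% | 15.0% | 10.0% | 5.0 |

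**Denominator 2: all randomised.** Let recurrence be 10% among successes in both arms. LAMS: 0.90 × 0.10 = 9.0%. DPPS: 0.75 × 0.10 = 7.5%. The arm with more failures shows fewer recurrences because failures cannot recur.

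**Failure or recurrence, all randomised.** With 10% recurrence in every success, LAMS: 0.10 + 0.90 × 0.10 = 19.0%. DPPS: 0.25 + 0.75 × 0.10 = 32.5%. Every randomised patient is counted, so the comparison keeps the protection of randomisation.

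**The Fig. 3 caption beside the rest.**
- *Lesion.* The caption says pancreatic pseudocyst; Table 1 enrols WON.
- *Window, read as within and after one month.* The first half comes before the assessment that establishes success. Table 2 requires symptoms needing intervention, and a change of treatment method in that month is already a drainage failure. One event could then count as both primary failure and recurrence.
- *Window, read as up to or at one month only.* The three- and six-month CTs would not serve the endpoint. Stent removal is given as 33 ± 3 days in the same caption, so the window would cover little beyond the time the stent is in place.

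**The case against.** **The document commits to no comparison.** It names no denominator, analysis set or test for recurrence; the Statistical analysis plan section covers baseline data, the primary outcome and adverse events. A reader might infer that a successes-only comparison is planned. The text does not say so, and an unseen analysis plan may settle it. That stands. What remains is that the event definition leaves neither obvious denominator neutral. It is fair to add that this belongs to recurrence as such, since a collection cannot recur before it resolves. The definition is not wrong in itself; it cannot carry a between-arm conclusion alone.

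**Fig. 3 contradicts Table 2.** A reader might infer this, but it is too strong. Table 2 gives no window, and its word for the lesion, cyst, does not exclude a pseudocyst. The conflict is with the WON population, the one-month success assessment and the failure rule. The caption may simply be garbled, and a collection that shrinks and reappears before the one-month visit is conceivable.

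**The size is assumed.** A reader might take the 7.5% against 5.0% row as a 50% relative excess that will be seen. The documents support no such figure. The bias is zero when b equals a, and its sign would reverse if b were below a. A 2.5-point difference is also small against the precision available: 1.96 × √(0.075 × 0.925/115.2 + 0.05 × 0.95/96) ≈ 6.5 points.

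**The composite can hide harm.** This stands. At a = 5% and b = 20%, failure or recurrence is 16.75% against 28.75%, and that 12-point gap comes wholly from the one-month difference. If DPPS recurrence is 5%, sustained success is 0.75 × 0.95 = 71.25%. LAMS recurrence among successes would have to reach 1 − 0.7125/0.90 = 20.8% before the arms looked equal.

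**Conclusion.** The point holds in a limited form. A between-arm comparison of recurrence as defined is not protected by randomisation, because being able to recur depends on a post-randomisation outcome expected to differ by 15 points (about 115 against 96 of 128). Under the assumed rates, selection alone gives a spurious LAMS excess of 0 to 5 percentage points among successes. This rests on two assumptions that the documents neither state nor test: that nobody succeeds with DPPS only, and that LAMS-only successes recur at least as often as the others.

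The Fig. 3 caption is a separate inconsistency, of lesion and of time, with the population, the success assessment and the follow-up schedule. Both matters concern a secondary endpoint. They limit what can be concluded about durability and nothing else.

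**What to change.** 1. Make the between-arm durability comparison one of sustained success in all randomised patients: clinical success at one month and no WON recurrence through the six-month visit, with one-month failures counted as not sustained.
2. Tabulate early failure and later recurrence separately by arm, and require the composite to be read with both.
3. Report recurrence among successes with its confidence interval, labelled as a non-randomised comparison.
4. Reconcile the Fig. 3 caption with Table 2 and the Outcomes text, so that recurrence means WON reappearing after the one-month success assessment and through the scheduled follow-up. Deleting only the within-one-month phrase is not enough, because it leaves recurrence tied to one month after the operation.

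The cost is wording in the protocol and analysis plan, using visits and CTs already scheduled. The drawback is that the composite is driven largely by the one-month difference and can mask a higher recurrence rate in the better-draining arm, which is why items 2 and 3 must accompany it.

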## Background

Walled-off necrosis (WON) is a type of pancreatic fluid collection (PFC) that develops in the setting of acute or chronic pancreatitis, trauma, or pancreatic duct obstruction [1]. WON, a delayed complication of necrotizing pancreatitis usually occurring > 4 weeks following the onset of pancreatitis, is PFC surrounded by a radiologically identifiable capsule containing both solid and liquid components [1]. Most WONs are asymptomatic and resolve spontaneously. However, drainage is necessary when it becomes symptomatic or infected, or increases in size over the course of the illness.

In the past decade, the treatment of symptomatic WON has evolved from surgical to endoscopic necrosectomy. Endoscopic treatment has a reduced proinflammatory response compared to surgery for the treatment of WONs [2]. It is associated with lower rates of pancreatic fistula formation and shorter hospital stays [3, 4]. Endoscopic ultrasonography (EUS)-guided drainage has high technical and clinical success and is associated with low adverse events (AEs) making it the optimal drainage approach for WONs [5, 6].

Double pigtail plastic stents (DPPS) is the standard choice for pancreatic pseudocyst drainage with > 90% technical and clinical success rates [5]. DPPS has also been used for WON drainage [7]. Recently, a novel lumen-apposing metal stent (LAMS) with a larger luminal diameter (≥ 10 mm) has been successfully used for EUS-guided drainage of PFC [8]. A multi-institutional consensus made by 22 expert endosonographers recommended that LAMS should be the standard of care for WON drainage [9].

However, the safety of LAMS is still controversial. Some studies have reported that LAMS is superior to DPPS in terms of overall treatment efficacy (90% vs 81%) and a significantly lower number of procedures (2.2 vs 3.6) [10]. LAMS includes single-step deployment and has an anti-migration structure [11, 12]. Other studies have proposed that LAMS was associated with a significantly higher rate of bleeding compared with DPPS [13–15]. Moreover, high quality of evidence with regards to the efficacy and safety of LAMS for WON drainage in Chinese patients is lacking. Given the recent widespread use of LAMS in the management of WON, we designed this open-label, prospective, parallel-group, superiority, multi-center randomized controlled trial (RCT) to investigate whether LAMS is superior to DPPS for WON drainage.

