## Discussion

The LVPWON trial has been designed to answer the question of whether LAMS is superior to DPPS for EUS-guided drainage of WON with regards to the clinical success rate and the incidence of AEs. We also want to prospectively investigate the risk factors for success of treatment and complications of EUS-guided drainage, which will provide a reference for the clinical treatment of WON.

EUS-guided drainage has been maturely applied in late PFC with well-defined inflammatory walls [7, 16–18]. Stents used for drainage are diverse. DPPS used in the management of PFC was first reported in the 1980s [19]. Subsequently, self-expanding metal stents (SEMS) and double-flanged LAMS have become the most popular drainage stents for PFC [8, 11, 12].

Due to their small diameter, several DPPSs are needed to achieve adequate drainage of a WON. Metal stents that have a larger diameter are theoretically considered superior to DPPS as they allow for the possibility of WON debridement. A previous study directly comparing DPPS and LAMS demonstrated that the latter had a success rate of 90%, which was higher than the former, and a significantly fewer number of procedures were required with LAMS for WON resolution [10]. In terms of AEs, stent occlusion seems more likely to occur in WON treated with DPPS [10]. Furthermore, new technology associated with LAMS enhance the drainage effect [20]. The procedure of LAMS deployment has become much easier and more economical.

However, with the increasing use of LAMS for WON drainage, LAMS-related bleeding has been more frequently reported [13–15]. In combined endoscopic and percutaneous drainage for symptomatic WON, LAMS did not reduce the time to percutaneous drain removal and was not associated with fewer AEs [21]. Furthermore, LAMS is substantially more expensive than DPPS.

Recently, a consensus guideline formulated by the Asian EUS group RAND/UCLA expert panel raised the issue of stent selection [5]. There are currently no randomized data addressing how LAMS compare with DPPS for WON drainage. An ongoing RCT observed serious LAMS-related AEs, including delayed bleeding in 50% of patients (6/12), buried stent syndrome, and biliary stricture [14]. However, our team had analyzed our center’s experience and determined that the use of LAMS is safe [22].

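### Table 2 makes the three bleeding criteria cumulative, so read literally some treated bleeds drop out of the between-arm bleeding comparison

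*Protocol article*

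**What the plan says.** Table 2 (Outcomes) gives one line per adverse event. Bleeding is "Any bleeding that requires intervention, blood transfusion, and hospital observation". Suprainfection is "Postoperative fever, increased inflammatory index (CRP, PCT), or positive blood culture". A residual row, Others, takes "Adverse events that occurred in the trial but not described above". No other section of the article defines either event.

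Adverse events are secondary: "The secondary outcome is technical success, operation time, recurrence, AEs, and secondary interventions". Under Statistical analysis plan, their incidence is compared between arms by a chi-square or Fisher's exact test.

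The article treats bleeding as the main doubt about the metal stent. The Background says other studies proposed that "LAMS was associated with a significantly higher rate of bleeding compared with DPPS". The Discussion cites an ongoing randomised trial with serious stent-related events, "including delayed bleeding in 50% of patients (6/12"), and frames the trial's question as superiority "with regards to the clinical success rate and the incidence of AEs".

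**The concern.** The bleeding row lists three consequences of a bleed and joins them cumulatively, while the suprainfection row just below it joins its list as alternatives. With the two side by side, a literal reader will take the difference as intended. On that reading the bleeding row keeps only events that needed both a procedure and a transfusion, with observation as well.

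At stake is the comparison that readers will look at first for safety. If bleeds are left out of the row, the recorded rates are too low in both arms. If some of the 18 hospitals apply the rule literally and others loosely, the rate also means different things at different centres.

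The suprainfection row leans the other way. A lone fever or a lone raised marker is enough, with no threshold and no comparison with the value before drainage. The Background names infection as one reason for drainage, and Table 1 does not exclude patients who already have fever or infection. A sign present beforehand could therefore be recorded as a new event.

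**Working it through.** **1. What the literal rule keeps and drops**

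| Bleed needed | Cumulative reading | Alternative reading |
|---|---|---|
| procedure + transfusion + observation | Bleeding | Bleeding |
| procedure + observation, no transfusion | not Bleeding | Bleeding |
| transfusion + observation, no procedure | not Bleeding | Bleeding |

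Patients return to the ward after drainage (Data collection and follow-up), so early bleeds meet the observation element almost automatically. The elements that decide are procedure and transfusion.

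**2. The plan's own figure**

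The article gives no adverse-event rate and claims no power for adverse events. Its only calculation is for the primary endpoint: 90% vs 75%, one-sided 0.025, power 85%.

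- Mean rate 0.825; √(2 × 0.825 × 0.175) = 0.5374; √(0.09 + 0.1875) = 0.5268.
- n = (1.960 × 0.5374 + 1.036 × 0.5268)² / 0.15² = 113.7, so 114 per arm.
- 114 / 0.9 = 126.7, so 127 per arm, against 128 stated.

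The figure reproduces to within one patient per arm. The bleeding definition does not enter it.

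**3. Effect on the bleeding comparison (all rates assumed)**

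Let the rates under the alternative reading be 15% (LAMS) and 5% (DPPS), and let a fraction f of bleeds in both arms meet all three elements. The recorded rates are 0.15f and 0.05f, and the recorded difference is 0.10f. With n = 128 per arm and two-sided 0.05:

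power = Φ{ [√n · |p1 − p2| − 1.96 √(2p̄(1 − p̄))] / √(p1(1 − p1) + p2(1 − p2)) }

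For f = 1: (1.131 − 0.832) / 0.418 = 0.717, and Φ(0.717) = 0.763.

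| f | Recorded rates | Difference (points) | Expected events | Power |
|---|---|---|---|---|
| 1 | 15% vs 5% | 10 | 19.2 vs 6.4 | 0.763 |
| 0.75 | 11.25% vs 3.75% | 7.5 | 14.4 vs 4.8 | 0.626 |
| 0.5 | 7.5% vs 2.5% | 5 | 9.6 vs 3.2 | 0.450 |
| 0.25 | 3.75% vs 1.25% | 2.5 | 4.8 vs 1.6 | 0.248 |

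Other assumed rates, for f = 1, 0.75, 0.5 and 0.25:

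- 10% vs 3%: 0.624, 0.496, 0.351, 0.196.
- 20% vs 5%: 0.957, 0.875, 0.700, 0.406.

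The normal approximation is rough where few events are expected.

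**4. Relative measure**

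With the same f in both arms, the risk ratio is 0.15f / 0.05f = 3 throughout. With different fractions it is 3 × f(LAMS) / f(DPPS):

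- 0.75 and 0.5 give 11.25% vs 2.5%, ratio 4.5, difference 8.75 points.
- 0.5 and 0.75 give 7.5% vs 3.75%, ratio 2, difference 3.75 points.

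The article gives neither fraction.

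**5. Suprainfection (all rates assumed)**

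Let true rates be 5% and 15%, and let a share q of uninfected patients show a lone sign. The recorded rate is p + (1 − p)q, and the difference shrinks by the factor (1 − q).

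| q | Recorded rates | Difference (points) | Power |
|---|---|---|---|
| 0 | 5% vs 15% | 10 | 0.763 |
| 0.1 | 14.5% vs 23.5% | 9 | 0.450 |
| 0.2 | 24% vs 32% | 8 | 0.296 |
| 0.3 | 33.5% vs 40.5% | 7 | 0.211 |

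**The case against.** The sponsor can say that the bleeding row opens with a word suggesting breadth, so the list may be a loose enumeration of what makes a bleed countable. This is a condensed article, and the full protocol and CRF may be clearer. That stands in part. The defect is an ambiguous rule with a likely direction, and a reader who infers that both adverse-event rates will certainly be wrong goes too far. But Table 2 is presented as the definitions, and nothing else in the article settles the reading.

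Second, the bleeds are not lost. The residual row takes events not described elsewhere, any later endoscopic operation is a secondary intervention, and treatment of stent-related events goes into the CRFs. This stands. The harm is misclassification within the bleeding row, not missing data.

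Third, a reader might infer that the definition tilts the trial towards calling LAMS safe. The documents do not support that as a relative bias. A common fraction leaves the risk ratio at 3, and if LAMS bleeds are more often severe, the literal rule would remove proportionately more DPPS bleeds and raise the ratio.

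Fourth, on suprainfection, the row's wording already implies timing and some increase, though it gives no reference value or cut-off. Two stronger inferences fail. That the rate would be saturated has no figure behind it. That unblinded staff would choose whom to test for CRP or PCT rests on the Fig. 3 footnotes, which itemise panels such as "hemoglobin (HGB), erythrocyte count (RBC), platelet count (PLT), leukocyte count (WBC), neutrophil percentage (%), lymphocyte percentage" and name neither marker. The body of that figure is not in the text available here, and a single-analyte row would need no footnote.

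Finally, the power figures use assumed rates for a secondary outcome with no stated power, so they contradict nothing in the plan. They are illustration only.

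**Conclusion.** The point holds in limited form. As written, the bleeding definition leaves out bleeds that needed a procedure or a transfusion but not both, and it can be read differently across centres. The recorded rate is then too low. If a similar fraction qualifies in both arms, the absolute difference shrinks by that fraction and power falls: from 76% to between 63% and 25% for assumed rates of 15% vs 5% and fractions from 75% to 25%. The direction under the literal reading follows from the wording. The size does not, because the article gives neither the bleeding rates nor the fraction. The direction of bias in relative terms is unknown.

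The suprainfection row is a lesser defect of the same kind: one sign is enough and there is no baseline reference, so over-counting is possible but its extent is unknown.

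This should be fixed but is not critical. Adverse events are secondary, and the primary endpoint, its analysis and the 256 patients are unaffected.

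**What to change.** **Bleeding.** State the elements in Table 2 as alternatives: intervention, or transfusion, or additional or prolonged hospital observation. The qualifier on observation is needed because patients are on the ward after the procedure anyway. Record each component in its own CRF field, so that the stricter all-three count can still be reported.

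**Suprainfection.** Require fever or a CRP or PCT elevation to be new or worse than the pre-procedure value, and apply the same written criteria in both arms. Let a positive blood culture count by itself. Requiring a clinical sign as well would exclude a culture-positive patient without one.

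**Timing.** Settle both before adverse-event data are compared between arms, including at the interim analysis planned at half enrolment. A later redefinition would look driven by results.

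**Cost.** Two lines of Table 2 and a few CRF fields. If CRP and PCT are not already measured before the procedure, they would have to be added to blood samples already scheduled. If centres would otherwise have applied the literal rule, the recorded bleeding rate will be higher. The sample size and primary analysis do not change.

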#### Data collection and follow-up

Investigators will save a recording of the operation and note the procedure time. After EUS-guided drainage, patients will be sent back to the ward. Patients will be monitored for 3 h and 24 h serum amylase after the operation and prophylactic antibiotics will be administered postoperatively. Detailed data information can be found in the SPIRIT figure (Fig. 3). After the LAMS is implanted, if the WON needs to be cleaned, direct endoscopic necrosectomy (DEN) will be performed. Stents will be removed one month after implantation. If the clinical success criterion is not met at the one-month follow-up, the patient will be provided with further treatment that will be decided based on their individual needs. All individuals who participated in the trial will be followed up at one, three, and six months post operation, with a final follow-up to occur 12 months after the end of the trial for CT evaluation. The above data will be collected into case report forms (CRFs). Stent-related AEs and management will also be recorded and reported in the CRFs. Finally, CRFs will be summarized by the National Clinical Research Center for Digestive Diseases.

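### Table 2 joins its three bleeding criteria with 'and', so a bleed needing intervention or transfusion alone leaves the bleeding row and the between-arm bleeding comparison undercounts

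*Protocol article*

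**What the plan says.** The Outcomes section lists adverse events among the secondary outcomes and refers to Table 2 for definitions. Four rows of that table matter here:

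- Bleeding: "Any bleeding that requires intervention, blood transfusion, and hospital observation".
- Suprainfection, the row directly below: "Postoperative fever, increased inflammatory index (CRP, PCT), or positive blood culture".
- Others, the residual adverse-event row: "Adverse events that occurred in the trial but not described above".
- Secondary intervention: "Any endoscopic operation after stent is placed".

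The statistical analysis plan section of the article says that adverse events are described by number and incidence and compared between groups with a chi-square or Fisher's exact test. Data collection and follow-up says that stent-related adverse events and their management go into the CRF.

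The Background reports studies in which "LAMS was associated with a significantly higher rate of bleeding compared with DPPS". The Discussion cites an ongoing randomised trial with delayed bleeding in 6 of 12 patients, and it makes adverse-event incidence part of the trial's question.

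**The concern.** The bleeding row is a list closed by 'and' under the verb 'requires'. Its plain meaning is that intervention, transfusion and hospital observation must all be needed. Two kinds of clinically relevant bleed then fail the row: one controlled endoscopically, radiologically or surgically without transfusion, and one transfused without any intervention.

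What is at stake is the one adverse event that the article singles out as the safety controversy about LAMS. If only part of the relevant bleeds reach the bleeding row, the estimated absolute excess is too small and the comparison has less chance of detecting a real one. A finding of no significant difference would then be hard to interpret.

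The wording may also be applied unevenly. The trial has 18 centres and unblinded endoscopists, and the central reading that the article describes is of CT images. Some centres may take the list as joint and others as alternatives, and the same bleed would be classified differently.

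**Working it through.** **1. The wording, row by row.** The suprainfection row uses 'or' where any one sign is enough. The perforation row, "Imaging manifests as pneumoperitoneum with peritoneal irritation syndrome", joins two findings that must occur together. The table therefore distinguishes alternatives from joint criteria, and the bleeding row carries the joint connective. No other section defines bleeding or says that one criterion is enough.

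**2. Where a non-qualifying bleed goes.**

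| Bleed | Bleeding row, as written | Others | Secondary intervention |
|---|---|---|---|
| Endoscopic haemostasis, no transfusion | no | yes | yes |
| Embolisation, no transfusion | no | yes | no (endoscopic operations only) |
| Transfusion, no intervention | no | yes | no |
| Intervention, transfusion and observation | yes | no | only if the intervention is endoscopic |

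The total adverse-event count need not change. The bleeding count does.

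**3. The plan's own figure.** Inputs from Sample size: 90% versus 75%, one-sided alpha 0.025, power 85%, dropout 10%. With a mean rate of 0.825:

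n = [1.960·√(2·0.825·0.175) + 1.036·√(0.90·0.10 + 0.75·0.25)]² / 0.15² = 113.7, so 114 per arm.

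114 / 0.90 = 126.7, so 127 per arm, against 128 stated. The figure reproduces to within one patient per arm. It concerns the primary endpoint only. The article states no bleeding rate and no power for bleeding.

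**4. Illustration of the loss.** Assumptions, none of them from the article: true rates of clinically relevant bleeding of 15% (LAMS) and 5% (DPPS), and a share s of those bleeds, equal in both arms, that meets all three criteria. The observed rates are 0.15s and 0.05s.

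- Risk ratio: 0.15s / 0.05s = 3 for every s.
- Risk difference: 0.10s.
- Power: exact enumeration of all 2×2 tables at 128 per arm, two-sided 0.05, with the likelihood-ratio chi-square, or Fisher's test when the expected event counts are below 5.

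| Share s | Expected bleeds, LAMS vs DPPS | Risk difference | Power |
|---|---|---|---|
| 1 | 19.2 vs 6.4 | 10.0 points | 79% |
| 3/4 | 14.4 vs 4.8 | 7.5 points | 66% |
| 1/2 | 9.6 vs 3.2 | 5.0 points | 47% |
| 1/3 | 6.4 vs 2.1 | 3.3 points | 26% |

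With assumed rates of 12% versus 4%, power is 69% when all bleeds count and 16% when a third do. A normal approximation at 15% versus 5% gives the same pattern: 76% at s = 1 and 45% at s = 1/2. The 128 per arm includes the dropout allowance. At 115 per arm (128 × 0.90), the approximation gives 72% and 41%.

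**5. If capture differs by arm.** Take 75% capture in LAMS and 40% in DPPS. The observed rates are 0.15 × 0.75 = 11.25% and 0.05 × 0.40 = 2.0%, the ratio rises to 5.6, and power rises from 79% to 90%. Swap the two shares and the rates are 6.0% and 3.75%, a ratio of 1.6. The definition alone does not fix the direction of any distortion.

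**The case against.** The strongest defence is that the 'and' is loose drafting. Read as alternatives, the row is sound: a bleed that needs an intervention, or a transfusion, or observation because of the bleed. That is close to the rewording proposed below. This stands as a possible intention, but nothing in the article states it, and the adjoining row points the other way.

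The defence also says that no data are lost. That is right. The residual row, the CRF record of management and, for endoscopic haemostasis, the secondary-intervention row all keep the event. The fault is one of classification within one secondary outcome, and it can probably be repaired from recorded data.

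A further defence is that the article condenses a fuller protocol. That would answer an omission. Here the article itself states the definition, so the wording can be judged as it stands.

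Three stronger readings might be inferred, and the documents do not support them:

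- *The rule makes LAMS look safer.* Equal capture leaves the risk ratio unchanged, and unequal capture can push it either way (step 5).
- *The row fails on either reading, because "After EUS-guided drainage, patients will be sent back to the ward" and every patient is therefore under observation.* The row speaks of bleeding that requires observation. A trivial ooze in a patient who is on the ward anyway does not meet that.
- *The comparison loses most of its power.* That depends wholly on the assumed share. At three quarters the fall is from 79% to 66%.

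**Conclusion.** The point holds as a defect of definition. Followed as written, the bleeding row excludes clinically relevant bleeds that needed an intervention or a transfusion but not both, and the between-arm bleeding comparison undercounts them. With equal capture, the absolute difference shrinks in proportion to the share captured and the risk ratio does not change. In the main illustration, power falls from 79% to between 66% and 26% as the share falls from three quarters to a third. Those figures rest on assumed bleeding rates and shares, so they show how the loss scales and do not predict its size in this trial.

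Bleeding is one row of a secondary outcome, and the protocol names no key safety endpoint. The primary endpoint and N = 256 are untouched. The wording should be corrected because bleeding is the article's own central safety question and the change is cheap, but it does not threaten the main result.

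**What to change.** Reword the outcome row so that the criteria are explicit alternatives, for example: bleeding after the start of the stent procedure that requires an endoscopic, radiological or surgical intervention, OR a blood transfusion, OR hospital admission or a prolonged stay because of the bleed. Give all 18 centres the same wording and apply it uniformly before bleeding is compared between arms. Report the three components separately by arm, from the adverse-event and management data that the CRF already collects. Events already entered under the residual row can be reclassified from those fields where the detail allows. This changes only how an outcome is counted and sets no rule for managing a bleed.

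The cost is one line in Table 2 and a few CRF tick boxes, with no added tests and no change to the sample size. The reported bleeding rate will be higher in both arms than under the literal rule, and the report should say so.
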